# Roxadustat in treating anemia in dialysis patients (ROAD): protocol and rationale of a multicenter prospective observational cohort study

**DOI:** 10.1186/s12882-021-02229-w

**Published:** 2021-01-13

**Keywords:** Roxadustat renal anemia hemodialysis

## Abstract

**Background:**

Roxadustat has been shown effective in treating patients with anemia due to chronic kidney disease. However, its long-term effect on clinical outcomes and socioeconomic burden and safety remains unclear.

**Methods/Design:**

This is a multicenter, prospective, longitudinal observational cohort study assessing if Roxadustat improves prognosis in dialysis patients. Primary outcomes will be major adverse cardiovascular events (MACE), defined as composites of cardiovascular death, myocardial infarction, cerebral infarction, hospitalization because of heart failure; all-cause mortality, and annual economic costs in two years. The data will be collected via Research electronic data capture (REDCap) based database as well as software-based dialysis registry of Sichuan province. The primary outcomes for the ROAD study participants will be compared with those in the dialysis registry cohort. Data at baseline and study follow up will also be compared to assess the association between Roxadustat and long-term clinical outcomes.

**Discussion:**

The main objective of this study is to the assess long-term association of Roxadustat on MACE, all-cause mortality, socio-economic burden, safety in dialysis patients, which will provide guidance for designing further large randomized controlled trials to investigate this clinic question.

**Study registration:**

The study has been registered in Chinese Clinical Trials Registry (ROAD, ROxadustat in treating Anemia in Dialysis patients, registration number ChiCTR1900025765) and provincial observational cohort database (Renal disEAse observational CoHort database, REACH, ChiCTR1900024926), registered 07 September 2019, http://www.chictr.org.cn.

## Background

The incidence and prevalence of Chronic kidney disease (CKD)is increasing globally which affects about 10% of people worldwide [1]. In China, the estimated number of people with CKD is 120 million [2], among which 2% will progress to end-stage renal disease (ESRD).

Renal anemia is one of the common complications of CKD especially ESRD, which is predominantly due to the reduction in erythropoietin (EPO) production by the kidney. Renal anemia can occur in any stages of CKD, but its prevalence and severity increases with the progression of CKD [3]. It is reported that more than 90% of dialysis patients have renal anemia [4], which is associated with increased risk of cardiovascular events [5, 6] and all-cause mortality [7].

Erythropoiesis-stimulating agents (ESA) are commonly used in the treatment of renal anemia. It can not only improve hemoglobin levels, but also cardiovascular outcomes in CKD patients. It can also delay the progression of chronic kidney disease, reduce hospitalization, all-cause mortality, and improve the quality of life of CKD patients [8]. The DOPPS study found that for every 10 g/L increase of hemoglobin (HGB), the risk of death and hospitalization decreased by 5% and 4% respectively [9]. However, the use of ESA also carries adverse events. For example, high dose of ESA is associated with increased risk of cardiovascular events and mortality, and regardless of HGB levels [10], demonstrated by the CHOICE study. In addition, ESA resistance can occur in some patients, resulting in treatment failure.

In recent years, hypoxia inducible factor (HIF) related medications have been tested in the treatment of renal anemia in a number of trials. HIF can increase the production of endogenous EPO by inhibiting the activity of prolyl hydroxylase. Roxadustat, as a HIF prolyl hydroxylase inhibitor (HIF-PHI), has been completed Clinical trials in several countries. The most recent randomized, multicenter, double-blind clinical studies, done in China, have found that Roxadustat significantly improved the hemoglobin level in CKD patients on and not on dialysis [8, 11]. Other studies also showed Roxadustat can effectively correct renal anemia, and reduce the requirements for blood transfusion and intravenous iron supplementation [3, 12, 13].

Despite the proven short-term benefits of Roxadustat in CKD patients, its long-term effect on clinical outcomes and socio-economic burden remains uncertain. Therefore, this study aims to perform a prospective longitudinal cohort study assessing the long-term effect of Roxadustat on cardiovascular events and mortality, as well as economic costs in dialysis patients with renal anemia.

## Methods/Design

### Study design

This is a multicenter, prospective, longitudinal cohort study. It has been registered in Chinese Clinical Trials Registry (ROAD, ROxadustat in treating Anemia in Dialysis patients, registration number ChiCTR1900025765), provincial observational cohort database (Renal disEAse observational CoHort database, REACH, ChiCTR1900024926).

### Study population

The participants included in the ROAD study will be patients with renal anemia in the context of end-stage kidney disease on dialysis (both hemodialysis and peritoneal dialysis), and on Roxadustat treatment who consent to the study. The de-identified data from the provincial dialysis registry of dialysis patients with renal anemia will be serves as a control group. The study was approved by the Institutional Review Board at Sichuan Provincial People’s Hospital (2019 − 196). The informed consent obtained from study participants will be written.

Inclusion criteria include:①Age 18–90 years; ②End-stage kidney disease patients who are receiving maintenance hemodialysis or peritoneal dialysis;③Dry weight 45–160 kg; ④Renal anemia, defined as HGB < 130 g/(male), HGB < 120 g/L(female) or HGB is maintained normal by ESA; ⑤willing to participate in the study with informed consent. Exclusion criteria includes:①patients with pre-existing malignancy; ②Known history of hematological disorders including myelodysplastic syndrome, multiple myeloma, hereditary hematologic disease such as thalassemia, sickle cell anemia, pure red cell aplasia, or other known causes for anemia other than CKD or dialysis. ③Patients who cannot complete the follow-up study.

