### Study outcomes

Primary outcomes will be major adverse cardiovascular events (MACE), defined as composite of cardiovascular death, myocardial infarction, cerebral infarction, hospitalization because of heart failure or unstable angina pectoris; all-cause mortality and annually medical economic costs in 2 years.

Secondary outcomes will include: ①Mean HGB changes from baseline to the 16th week and percentage of patients within HGB treatment target (110–130 g/L). ②Changes from baseline and variations in the mean HGB level throughout the whole study periods (up to 108 weeks). ③Changes of serum iron metabolism indexes (Hepcidin, ferritin, transferrin, transferrin saturation, and total iron binding capacity) as well as requirements for intravenous iron replacement from baseline to the end of the study(up to 108 weeks). ④Changes of blood pressure and antihypertensive medications from baseline to 16th week. ⑤Changes of serum lipids profile from baseline to 16th week. ⑥Changes of the following laboratory results (collected in the Sichuan provincial dialysis registration system) from baseline to the end of study, dialysis related parameters, dialysis adequacy and chronic kidney disease- mineral bone disorder (CKD-MBD) markers (serum phosphorus, calcium, and parathyroid hormone). ⑦Mean weekly dosage of Roxadustat to maintain HGB within the treatment target. ⑧Adverse events (AE) during the follow-up period, with a focus on drug discontinuation due to AE. ⑨Annual economic cost related to hospitalization, outpatient treatments, medical insurance coverage and out-of-pocket payments.

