### Data collection

The de-identified data were collected in REACH via Research electronic data capture (REDCap [14, 15], hosted at Sichuan Provincial People’s Hospital) pre-designed forms from baseline to week 108/2 years. The table with an identification code will be kept within the study site in a secure way. The provision of de-identified medical records will be required for judication for the MACE outcome. Participants will be followed up to 2 years except that they withdraw from the study, have their dialysis type changed, receive kidney transplantation or have lost follow up.

Dialysis data from each study site in the provincial dialysis registry will be collected via a dialysis software provided by the Sichuan Quality Control Center of Renal Disease at the end of the first and second study year.

A questionnaire focusing on medical expense for the participants will be collected at the end of the first and second year of the study.

The target sample size of the ROAD participant is greater than 250 basing on the MACE incidence of at least 20% [16, 17] within 2 years among ROAD and dialysis registry cohort, basing on noninferiority assumption with a marginal difference of 0.02 (10% of MACE incidence), actual difference of -0.08 (40% of MACE incidence),α = 0.05 and 1-β = 0.8, allowing a drop rate of 15%, using ‘Non-Inferiority Tests for the Difference Between Two Proportions’ of PASS software 15.0.5.

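### As printed, ROAD entry allows patients already on Roxadustat, and the registry control has no non-use condition, no exclusion of ROAD participants and no matched start of follow-up

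*Protocol article*

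**What the plan says.** All references are to the Methods/Design part of the protocol article.

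- **Exposed group (Study population).** Participants are dialysis patients with renal anemia "and on Roxadustat treatment who consent to the study". The five inclusion and three exclusion criteria set no first-dose date, new-start condition or limit on earlier treatment. One exclusion removes patients who cannot complete follow-up.
- **Control (Study population).** "The de-identified data from the provincial dialysis registry of dialysis patients with renal anemia will be serves as a control group". Nothing is said about Roxadustat use in these patients, about an index date, or about whether ROAD participants are taken out.
- **Shared source (Study outcomes, Data collection).** Some of ROAD's own laboratory outcomes are "collected in the Sichuan provincial dialysis registration system". For the registry, "Dialysis data from each study site in the provincial dialysis registry will be collected via a dialysis software".
- **Timing (Data collection).** ROAD data are entered on "pre-designed forms from baseline to week 108/2 years". Registry data are collected "at the end of the first and second study year". Baseline is not tied to the first dose, and no start of risk time is given for controls.
- **Test and size (Data collection).** The target of more than 250 ROAD participants rests on a "MACE incidence of at least 20" percent within 2 years and a "noninferiority assumption with a marginal difference of 0.02 (10% of MACE incidence"), with an assumed true difference of -0.08.
- **Analysis (Data analysis).** The primary outcomes are compared by multivariable Cox regression, with a propensity-score method as sensitivity analysis.

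**The concern.** A cohort comparison needs three things settled before any model is fitted: who counts as exposed, who counts as unexposed, and when the clock starts in each group. The article prints the first two in a form that does not separate the groups, and gives no start common to both.

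If patients may enter after any length of treatment, those who died, failed or stopped early on the drug are under-represented in ROAD. The observed ROAD risk is then too low. If registry controls may be on Roxadustat, or may be the ROAD participants themselves, part of the control carries the exposed group's risk and the difference shrinks toward zero. Under the planned benefit this costs power. Under true harm it hides some of the harm, which is the wrong direction for a non-inferiority comparison.

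Covariate adjustment does not cure either problem. Neither the Cox model nor a propensity score brings back early failures who never entered, removes exposed patients from the control, or creates a time zero. The margin is 2 percentage points, so modest distortions matter.

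A further consequence concerns the HGB outcomes: for a patient already on treatment at entry, the baseline value is not a pre-treatment value.

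**Working it through.** **Inputs from the article (Data collection):** control 2-year MACE risk 0.20; assumed difference -0.08, so ROAD 0.12; margin 0.02; alpha 0.05, sidedness not stated; power 0.80; dropout 15%.

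**Assumed, because the documents give no value:** the share c of Roxadustat users in the control, and the relative reduction s in observed ROAD risk caused by selection. The calculations use unadjusted proportions.

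**Step 1: the plan's own figure.** With equal groups and one-sided 0.025:

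n = (1.960 + 0.842)² × (0.12×0.88 + 0.20×0.80) / (0.02 + 0.08)² = 7.849 × 0.2656 / 0.01 = 208.5, so 209 per group.

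Allowing for dropout, 209/0.85 gives 246. The Farrington-Manning score version gives 212, and 212/0.85 gives 250. At one-sided 0.05 the result is 165, or 195 after dropout. The printed target therefore reproduces with 0.05 read as two-sided. The sample-size figure is not in question on this point.

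**Step 2: formula for the illustrations.**

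P(declare non-inferiority) = Φ{[0.02 − (pT − pC)] / SE − 1.960}, with SE = √{[pT(1−pT) + pC(1−pC)] / 209}.

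**Step 3: contamination under the planned benefit.** pT = 0.12 and pC = 0.20 − 0.08c. For c = 0.2: pC = 0.184, the difference is -0.064, SE = √(0.2557/209) = 0.0350, and Φ(0.084/0.0350 − 1.960) = 67.1%.

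**Step 4: contamination with true harm at the margin.** pT = 0.22 and pC = 0.20 + 0.02c. For c = 0.2: pC = 0.204, SE = 0.0400, and Φ(0.004/0.0400 − 1.960) = 3.1%.

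| c | Observed difference, planned benefit | Power | ROAD number for 80% power, with dropout | False non-inferiority, harm at margin |
|---|---|---|---|---|
| 0 | -0.080 | 80.1% | 246 | 2.5% |
| 10% | -0.072 | 74.0% | 285 | 2.8% |
| 20% | -0.064 | 67.1% | 336 | 3.1% |
| 30% | -0.056 | 59.3% | 402 | 3.5% |
| 50% | -0.040 | 42.5% | 617 | 4.4% |

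**Step 5: selection with true harm at the margin.** pT = 0.22(1 − s) and pC = 0.20. For s = 10%: pT = 0.198, SE = 0.0391, and Φ(0.022/0.0391 − 1.960) = 8.1%.

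| s | Observed ROAD risk | False non-inferiority |
|---|---|---|
| 0 | 0.220 | 2.5% |
| 5% | 0.209 | 4.6% |
| 10% | 0.198 | 8.1% |
| 20% | 0.176 | 20.9% |
| 30% | 0.154 | 42.5% |

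**Step 6: immortal time, a conditional case only.** Suppose follow-up ran for 24 months from the first dose, pre-consent months were counted as risk time, and the drug had no effect. With h = −ln(0.8)/2 = 0.1116 per year, the risk with m event-free months is 1 − exp[−h(24 − m)/12]. This gives 17.7% for m = 3 and 15.4% for m = 6, which is 2.3 and 4.6 points below 20%. If follow-up starts at enrolment, this component is zero.

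**The case against.** Several points on the other side are sound.

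- **Starters may be intended.** A reader might infer that ROAD does enrol long-term users. The text does not show that. HGB, blood pressure and lipid changes from baseline to week 16, and eligibility through HGB kept normal by ESA, fit patients starting the drug. What stands is that no criterion requires it.
- **Overlap is permitted, not shown.** A reader might infer that ROAD participants are counted as their own controls. A shared data source is not a shared analysis set, and the Data analysis section names two groups. Yet the only printed definition of the control admits them, along with users who did not consent.
- **The registry timing says little.** Collection at the end of each study year tells us when data are gathered. It does not mean that controls' follow-up starts then.
- **The immortal-time shifts do not apply as a default.** It is tempting to set 2.3 and 4.6 points against the 2-point margin. The article describes forms completed from baseline, and those figures need follow-up dated from the first dose without delayed entry.
- **Controls are survivors too.** They are already on dialysis when observed, so only the difference in selection between the groups matters, and its size is unknown. The exclusion of patients who cannot complete follow-up has no stated counterpart for controls.
- **Contamination inflates error only a little.** At the margin it moves false non-inferiority from 2.5% to 4.4% even at 50% users. Its main cost is power.
- **The full protocol or SAP may settle dates and duplicates.** That is possible. But the exposed and control definitions are printed here, and following them as printed does not separate the groups.

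**Conclusion.** The point holds as an exposure to bias that the printed definitions create. It is not a demonstrated bias of known size. Entry allows prior Roxadustat treatment of any length. The control is not limited to non-users, does not exclude ROAD participants, and has no start of follow-up matched to ROAD's baseline.

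The two mechanisms differ. Selection of survivors and tolerators favours Roxadustat and, in the illustrations, is the more serious threat to the non-inferiority error rate. Contamination pulls toward zero and mainly erodes power. All these figures rest on assumed values of c and s, 209 evaluable patients per group, one-sided 0.025 and unadjusted proportions. They show how sensitive a 0.02 margin is, not what will happen in ROAD.

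MACE and all-cause mortality both depend on this comparison, and the definitions can be corrected in wording and data handling, so this should be settled before analysis.

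**What to change.** 1. **Control.** Define it as registry patients who meet the same age, dry-weight, anemia and exclusion criteria and are not on Roxadustat at their index date. Remove ROAD participants.
2. **Time zero.** Record each ROAD patient's first-dose date. Start risk time at enrolment, or at first dose with delayed entry at enrolment. Give controls an index date on the same calendar date while alive on dialysis.
3. **New starters.** Make them the main comparison, or at minimum a pre-specified analysis, and report earlier starters separately. For HGB change, use a pre-dose value as baseline.
4. **Later switching.** Add a sensitivity analysis that censors controls when they start Roxadustat.

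If only starters are meant to be enrolled, one sentence saying so settles the new-start part of item 3.

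**Cost.** The changes are to wording and data handling; treatment is untouched. Roxadustat use and start dates must be obtainable from the registry or the sites, which the article does not confirm. Some prevalent users would leave the main comparison, with a loss of precision that depends on their unknown share. A larger control could offset this. With two controls per ROAD patient and the plan's own assumptions, 7.849 × (0.1056 + 0.16/2) / 0.01 = 145.7, so 146 evaluable ROAD patients, or 172 after 15% dropout, would keep 80% power.

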### Data analysis

The comparison in primary outcomes between the ROAD cohort and the registry data will be performed using Multiple Cox regression of risk factors and propensity score method will also be applied as a sensitivity analysis. The medical economic costs will be compared between ROAD cohort and registry control group using the whole population as well as populations stratified by hospital levels, regions, comorbidities.

The efficacy on HGB of Roxadustat in the treatment of anemia of the whole cohort as well as the pre-defined subgroups (including patients with evidence of erythropoietin resistance, patients with chronic inflammation, patients with impaired iron metabolism, and patients on hemodialysis or peritoneal dialysis) will be analyzed in intention-to-treat and per-protocol ROAD population. Treatment heterogeneity will be tested by adding an interaction term to the statistical models.

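### The age, dry-weight, malignancy and haematology limits set for ROAD patients are not applied to the registry control, so the primary comparisons may set a restricted cohort against a broader one

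*Protocol article*

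**What the plan says.** The Study population section defines the two groups in consecutive sentences. ROAD participants are anaemic dialysis patients "and on Roxadustat treatment who consent to the study". The comparator is given separately: "The de-identified data from the provincial dialysis registry of dialysis patients with renal anemia will be serves as a control group".

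A numbered list follows:

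- Inclusion: (1) age 18–90; (2) maintenance haemodialysis or peritoneal dialysis; (3) dry weight 45–160 kg; (4) renal anaemia by haemoglobin threshold, or haemoglobin held normal by an ESA; (5) informed consent.
- Exclusion: (1) pre-existing malignancy; (2) haematological disorders and other known causes of anaemia; (3) inability to complete follow-up.

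The section does not say whether the list covers the registry patients.

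The abstract's Methods/Design paragraph states the main contrast: "The primary outcomes for the ROAD study participants will be compared with those in the dialysis registry cohort". The Data analysis section assigns it to "Multiple Cox regression of risk factors and propensity score method will also be applied as a sensitivity analysis". On cost it says: "The medical economic costs will be compared between ROAD cohort and registry control group using the whole population"; the same sentence goes on to add comparisons stratified by hospital level, region and comorbidity.

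**The concern.** Two items on the list, consent and ability to complete follow-up, cannot be carried over to de-identified registry records. Taken as it stands, the list therefore describes ROAD enrolment, and the control keeps only its own shorter definition. A programmer who followed the text would extract every registry dialysis patient with renal anaemia, including any with cancer or a dry weight below 45 kg.

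Such patients plausibly die more often and cost more. If they are present only among controls, part of any difference in mortality or cost would reflect who was allowed into each group and not the drug. All three primary outcomes rest on this comparison. Aligning the start of follow-up, or choosing controls who do not take Roxadustat, would not remove the mismatch.

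**Working it through.** **1. The two definitions side by side**

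| Criterion | ROAD | Registry control, as stated |
|---|---|---|
| On dialysis | yes | yes |
| Renal anaemia | yes, with thresholds | yes, no thresholds given |
| Age 18–90 | yes | not stated |
| Dry weight 45–160 kg | yes | not stated |
| No pre-existing malignancy | yes | not stated |
| No haematological or other cause of anaemia | yes | partly implied by the word renal |
| Consent; able to complete follow-up | yes | cannot be applied as written |

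**2. The plan's own yardstick**

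The sample-size paragraph (Data collection) gives "MACE incidence of at least 20" per cent within 2 years, a margin of 0.02, an assumed true difference of −0.08, α = 0.05, power 0.80, 15% dropout and a target above 250.

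With risks of 0.20 and 0.12, the distance to the margin is 0.08 + 0.02 = 0.10. With 1:1 groups (assumed) and one-sided 0.025:

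n = [0.20×0.80 + 0.12×0.88] × (1.960 + 0.842)² / 0.10² = 0.2656 × 7.849 / 0.01 = 208.5, so 209 per group; 209/0.85 = 245.9, so 246.

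The pooled-variance form gives 211, then 249. Both agree with the stated target when α is read as two-sided. One-sided 0.05 gives 165, then 195, which does not. The target is not affected by this point. The margin of 2 percentage points is the scale against which to judge a distortion.

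**3. Crude distortion from the mismatch alone**

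Assumptions, not in the documents: ROAD-eligible patients have a 20% two-year risk in both groups, and a share f of controls is ineligible at r times that risk.

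Control risk = 0.20 × [1 + f(r − 1)]

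| f | r = 1.5 | r = 2 |
|---|---|---|
| 5% | 20.5% | 21% |
| 10% | 21% | 22% |
| 20% | 22% | 24% |

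Subtracting 20% gives 0.5 to 4 points in Roxadustat's favour with no true difference. The 2-point margin is reached at f = 10%, r = 2 and at f = 20%, r = 1.5.

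**4. What that could do to a non-inferiority claim**

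Take a true excess exactly at the margin (22% against 20% among eligible patients), about 212 evaluable ROAD patients (250 × 0.85 = 212.5), one-sided 0.025 and r = 2. For f = 10% and 1:1:

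- Control risk is 0.22 and the expected crude difference is 0.
- SE = √(2 × 0.22 × 0.78/212) = 0.0402.
- Rate of a false claim = Φ(0.02/0.0402 − 1.96) = 7.2%, against a nominal 2.5%.

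| f | 1:1 | registry 10 times larger |
|---|---|---|
| 5% | 4.4% | 5.2% |
| 10% | 7.2% | 9.9% |
| 20% | 16.3% | 26.7% |

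These are unadjusted comparisons, so they show what is possible and do not predict the planned Cox result.

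**5. Can adjustment repair it?**

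Simulation: 250 ROAD patients, 2,500 controls, true hazard ratio 1.0, ineligible controls at hazard ratio 2, one other covariate, 200 runs per setting.

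| Ineligible share | Indicator omitted | Indicator in Cox model | Ineligible controls removed |
|---|---|---|---|
| 10% | 0.93 | 1.015 | 1.015 |
| 20% | 0.86 | 1.01 | 1.01 |

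Where the condition is recorded and modelled as an indicator, adjustment and restriction agree. Where it is left out, the bias remains.

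**The case against.** The strongest reply is that the text is silent, not wrong. The Study population heading covers both groups, and the list does not say that it is for ROAD only. Being on Roxadustat, the feature that defines ROAD, is not one of the numbered items. The consent item shows only that this item cannot apply to the registry, not that the others do not. A condensed article may also leave the extraction filter to a fuller document.

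This stands in part. A reader might infer that the controls definitely include patients with cancer or low weight; the documents do not say so. But the article gives the control a definition of its own that differs from ROAD's. That is a stated design feature and more than missing detail.

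Three other stronger readings also fail:

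- *Adjustment cannot help because the groups do not overlap.* The simulation contradicts this for a recorded condition entered as an indicator, and propensity matching would likewise leave such controls unmatched. Dry weight would need a cut-point or a correct functional form. What survives is that the Data analysis section names no such covariates, and that the cost comparison uses the whole population alongside its comorbidity strata.
- *The bias always favours Roxadustat.* It is plausible for mortality and cost. For MACE, a non-cardiovascular cancer death is not an event and competes with it, and any controls under 18 may carry lower risk.
- *Controls carry every other cause of anaemia.* Requiring renal anaemia already removes many of these.

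A fair practical objection is that the documents do not say whether the registry records malignancy or dry weight. If it does not, neither a filter nor a covariate is available.

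**Conclusion.** The point holds as a mismatch in stated eligibility. The article restricts ROAD by age, dry weight, malignancy and haematological disease and states no such restriction for the control, although all three primary outcomes are compared across the two groups. The likely direction favours Roxadustat for mortality and cost and is uncertain for MACE.

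The crude illustration of 0.5–4 points rests on assumed ineligible shares of 5–20%, assumed risk ratios of 1.5–2, and the plan's 20% event risk applied to eligible patients. It shows that the mismatch could reach the 2-point margin, not that it will. The bias in the planned Cox analysis could be much smaller if the excluded conditions are recorded and modelled, but the article does not commit to that.

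**What to change.** In the Study population section, state that inclusion criteria 1–4 and exclusion criteria 1–2 are applied to registry records at each control's start of follow-up, and that all primary comparisons, including the whole-population cost comparison, use only controls who meet them. Consent and ability to complete follow-up cannot be imposed on registry records as written and should be acknowledged as remaining differences.

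For any criterion that the registry does not record, name it as a limitation and add a sensitivity analysis that bounds its effect over a stated range of shares and risk ratios.

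The cost is a short addition to the text and a filter on registry data, provided the variables exist. The control group becomes smaller, and some records will be lost where weight or history is missing. The ROAD target of more than 250 does not change.
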